### Participant eligibility criteria

The inclusion criteria will be household members ≥20 years old and pregnant women who willingly agree to exclusively use MAR water during the dry season for drinking and cooking purposes. The Dhaka University team have determined the catchment area for each MAR site based on geographical distance from MAR infrastructure and have developed a list of households who expressed willingness to drink MAR water. Any ≥20-year-old hypertensive household members will be also eligible for participation but research staff will collect information about their medication if any. Research staff will enrol postadolescent ≥20-year population as an individual’s response to salt intake (salt-sensitivity) increases with age^55^ and adolescence is associated with adrenal and nervous system maturation that may contribute to salt sensitivity.^56 57^ They will approach households living near the MAR water access point. They will enrol the 28 closest households surrounding each MAR system that meet the inclusion criteria and consent (online supplementary information 1) to study participation. During the informed written consent process, research staff will inform each household that they will be randomly selected when to start consuming MAR water as part of the scientific process of the study. All household members >20 years of age will be eligible and enrolled in the study from the selected 28 households. In addition, research staff will enrol households that include a pregnant woman in each selected MAR catchment community irrespective of household selection from a list of pregnant women developed by a female promoter.

10.1136/bmjopen-2016-015205.supp1Supplementary file 1

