### Randomisation and intervention delivery

We will randomly select four MAR communities to drink MAR water in each step following the first (baseline) step (figure 3) by computer-generated random numbers. Randomisation will be conducted by an investigator who will not be directly involved in implementation of the stepped-wedge study and this will be done before commencement of the study. The study could not be blinded, therefore there was no concealment from the cluster participants. Although infiltration of rainwater and pond water into the brackish aquifer through the MAR systems will be ongoing for 1–2 years in each community, people will not have access to MAR water until a formal handover of MAR systems to community members. The implementers hire a caretaker or gatekeeper for each MAR community who is responsible for maintenance of the respective MAR system prior to the community handover. The implementers form a community management team who are responsible for maintenance of each MAR system following handover. We have synchronised the community handover with the randomisation schedule in the 16 communities after consulting with the gatekeepers. Community health promoters will inform the participants when the MAR water will be available for consumption once the community management team is formed. Agreement of the implementers and gatekeepers was sought at the beginning of the study during site selection for inclusion of any site in trial and access of MAR water as per the randomisation.

We will deploy a local trained promoter at each MAR site, who will visit these households, list members and identify pregnant women in these and other households in catchment areas of each MAR site. Promoters will encourage all household members to drink MAR water exclusively while they are at home, carry a bottle of MAR water while they go out for work and other activities, and to cook with MAR water. The community health promoters will visit households with promotional materials (eg, flip charts) from the beginning of the study to inform household members about adverse health effects of drinking brackish water and potential benefits of drinking low-salinity MAR water. As per the randomisation schedule, they will inform households when MAR water will be available for consumption.

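### The protocol treats allocation concealment as impossible because blinding was impossible, and so leaves willingness- and consent-based enrolment open to selection by handover order

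*Protocol article*

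**What the plan says.** Under Randomisation and intervention delivery, the protocol article has an investigator outside day-to-day implementation draw the order by computer, and "this will be done before commencement of the study". Its only statement on concealment is "The study could not be blinded, therefore there was no concealment from the cluster participants". The same section adds: "We have synchronised the community handover with the randomisation schedule in the 16 communities after consulting with the gatekeepers". Promoters list household members, identify pregnant women, encourage use of MAR water and announce when it becomes available.

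Under Participant eligibility criteria, participants are adults and pregnant women "who willingly agree to exclusively use MAR water during the dry season for drinking and cooking purposes". The implementing university's team "have developed a list of households who expressed willingness to drink MAR water". For research staff the rule is: "They will enrol the 28 closest households surrounding each MAR system that meet the inclusion criteria and consent". At consent, "research staff will inform each household that they will be randomly selected when to start consuming MAR water". Pregnant women are added from a promoter's list, whether or not their household is among the 28. Under Statistical methods they are included in the primary analysis, with few expected.

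**The concern.** The sentence on concealment gives a reason that does not support it. Once water is available everyone will know, so blinding is out of reach. That does not prevent the order from being held back until the people to be analysed have been listed, have consented and have been measured at baseline.

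This matters because enrolment is voluntary and rests on a promise of behaviour. Agreeing to use MAR water exclusively may mean something different to a household expecting it next month than to one expecting it at the last step. If households or recruiters know the order, refusals and keenness can differ by sequence. Two consequences should be kept apart:

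- A constant difference in blood pressure between sequences, which crossover and the random effects largely absorb.
- A difference in uptake or response between sequences, which they do not. Early sequences supply all the longest-exposure data, so this would weigh most on the secondary analysis of time to effect.

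**Working it through.** **Reading the text**

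1. *Draw before enrolment?* The article says before the study starts. That most naturally means before consent and visit 1, but it is not said in those words.
2. *Who knows the order?* Gatekeepers are consulted on handover under the schedule, and promoters pass on the date. When promoters learn it is not stated. No sentence says that it is withheld from anyone until enrolment ends.
3. *What is left to choice?* The 28 households are the nearest that qualify and consent, out of 60–70 per catchment: 28/70 = 40% to 28/60 = 47%. If a household declines, the next nearest can take its place. Staff discretion is limited; self-selection is not.
4. *Pregnant women.* They fall outside the nearest-household rule and are identified by promoters, who also announce availability.

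**Size of a constant sequence difference (illustration)**

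The article gives no figure for selection bias. The yardstick is its planned effect of 3 mm Hg with SD 20. The stated unadjusted sample size reproduces: 2 × 20² × (1.960 + 0.842)² / 3² gives 698 per arm, 1396 in total.

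Inputs from the article: 16 communities, 5 visits, 4 communities crossing over per step, 60 people per community, total variance 20² = 400. Assumed: enrolment shifts mean systolic pressure by 1 mm Hg per sequence (d = −1.5, −0.5, 0.5, 1.5, so 3 mm Hg from first to last), constant over time. The ICC is not stated and is varied from 0.01 to 0.10. The share of the remaining variance that is stable within a person is also assumed (0, 0.5 or 0.7). A separate household effect is left out.

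In a generalised least squares fit with period effects:

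- Total sum of squares of the treatment indicator after removing period means: 16 × (0 + 3/16 + 4/16 + 3/16 + 0) = 10.
- Between-community part: 5 × 4 × Σ(d/5)² = 20 × 5/25 = 4. The within-community part is 10 − 4 = 6.
- Cross-product of community-mean treatment with the shift: 5 × 4 × Σ(−d/5)(d) = −20.
- Weight on between-community information: λ = σe² / (σe² + 5σc²), where σc² = community variance + (stable person variance)/60, and σe² = (residual variance)/60.
- Bias = −20λ / (6 + 4λ).

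Worked cases at ICC 0.01 (community variance 4, remainder 396):

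- No stable person variance: σc² = 4, σe² = 396/60 = 6.6, λ = 6.6/26.6 = 0.248, bias = −4.96/6.99 = −0.71.
- Half stable: σc² = 4 + 198/60 = 7.3, σe² = 3.3, λ = 3.3/39.8 = 0.083, bias = −1.66/6.33 = −0.26.

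Absolute bias in mm Hg:

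| ICC | share 0 | share 0.5 | share 0.7 |
|---|---|---|---|
| 0.01 | 0.71 | 0.26 | 0.14 |
| 0.02 | 0.43 | 0.18 | 0.10 |
| 0.05 | 0.19 | 0.09 | 0.05 |
| 0.10 | 0.10 | 0.05 | 0.03 |

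At an ICC of exactly 0 the row would be 2.00, 0.50 and 0.25. The sign follows the direction of the assumed gradient. The zero-share column describes different people at each visit, which is not this trial: it follows the same participants and plans participant random effects.

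**Selection on uptake or response** is not captured by this calculation. The article gives no uptake by sequence from which to size it.

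**The case against.** The strongest reply is that the safeguards already in the text close most routes. Household willingness had been listed by the implementer, and the article reports that in the past while the draw is still in the future. Nearest-first enrolment stops staff from picking keen households. Households are told at consent that their start is random, with no date mentioned, and the announcement follows the forming of the management team, which suggests disclosure near handover. The concealment sentence may mean only that participants know whether they are receiving MAR water.

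Much of this stands, and it rules out several stronger readings that a reader might infer:

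- *That enrolling staff hold the schedule, or that households know their date at consent.* Neither is stated. Gatekeepers are described as maintaining the systems, not as enrolling anyone.
- *That willingness is judged entirely after the draw.* The household list already exists; individual agreement and consent remain.
- *That late communities wait until the end of the dry season.* No trial calendar is given. The last group starts three monthly steps after the first.
- *That a bias can be computed from assumed uptake rates.* Any such rates would be invented, and the result would be a difference in effect between sequences, not bias in the primary estimate.
- *That the missing enrolment cut-off for pregnant women is itself an error.* An article may leave that to the full protocol.

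What the reply does not remove is the faulty inference and its consequence. The only sentence on concealment says there was none, and a trial team following it has no reason to hold the order back. The safeguards do not prevent refusal by sequence, nor do they cover pregnant women.

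**Conclusion.** The point holds as a correctable flaw in the design as stated: lack of concealment is wrongly derived from lack of blinding, and participation could depend on sequence through individual agreement, consent and the promoter's list of pregnant women.

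Bias in the primary intention-to-treat estimate is probably modest. Under the assumed 3 mm Hg gradient, with half of the non-community variance stable within person, it is 0.05 to 0.26 mm Hg, about 2% to 9% of the 3 mm Hg target. The upper figure of 0.71 (24%) needs a low ICC and no within-person correlation. The gradient, ICC and within-person share are all assumptions; the document gives none of them. Selection on uptake or response is less well protected, and its size cannot be estimated from the document. The conclusion also assumes that starting the study includes enrolment, which is the natural reading but is not explicit.

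**What to change.** Replace the sentence on concealment so that the two ideas are separate, for example:

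*Participants and field staff cannot be blinded once access begins. The investigator who generates the order will withhold it from enrolling staff, promoters and households until listing, consent and visit 1 are complete in all 16 communities. Implementers and gatekeepers will receive only the notice needed for handover and will undertake not to disclose it.*

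The design leaves room for this, since no community has access during the first monthly step.

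For each pregnant woman, record whether she was enrolled before or after the order was disclosed or handover took place, and add a sensitivity analysis without those enrolled after.

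If the order has already been disclosed, say who knew it and when, and report refusals, baseline characteristics and uptake by sequence.

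The cost is tighter control of information and somewhat shorter notice in the field. The agreed handover plan is unchanged and no extra measurements are needed; the added work is one recorded item, one sensitivity analysis and, if disclosure has occurred, the reporting by sequence.

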### Sample size

The sample size of the stepped-wedge trial was calculated based on the effect of MAR systems to reduce systolic blood pressure of the ≥20-year-old community members. Data from southwest coastal Bangladesh demonstrated a 7 mm Hg lower mean systolic blood pressure among pregnant women who drank pond water compared with those who drank brackish water, and a 17 mm Hg lower mean systolic blood pressure for pregnant women who drank rainwater compared with those who drank brackish water.^35^ The mean reduction in systolic blood pressure following long-term modest salt reduction is 4.2 mm Hg.^50^ For calculations, we considered a mean systolic blood pressure reduction of at least 3 mm Hg among the communities who will have access to MAR water for drinking and cooking purposes compared with those who will use brackish water. The entire population under the MAR community catchment area will be considered as one cluster. Each MAR community serves approximately 300 people, constituting 60–70 households in the catchment area.^28^ The mean household size in southwest coastal Bangladesh is 4.2, approximately 52% of household members are ≥20 years old.^58 59^ Since we will collect blood pressure from all household members ≥20 years old, we estimated an average of 2.2 participants in this age group per household. We will select 28 households per cluster (28×2.2=60 people per cluster). A previously published study in Bangladesh reported SD 13.51 for systolic blood pressure,^60^ but we considered SD 20 for systolic blood pressure to capture a greater variation of blood pressure. We calculated the sample size for the stepped-wedge trial adopting the formula used by Hussey and Hughes.^61^ Although their formula assumed no within-participant correlation over time (cross-sectional design), we applied their formula for a cohort design (same participant followed up over time). The salinity problem and the MAR water quality may be influenced by seasonality over the progression of dry season and participants’ blood pressure may respond differently to different level of sodium exposure in MAR drinking water. Therefore, it is important that we investigate the effect of the MAR system on the same participants over the entire dry season. Since we will investigate the same participants in each step, we will have less participant-level variability and sufficient power compared with a cross-sectional design to investigate the effect of MAR systems. We initially calculated the sample size for a simple unadjusted trial (N_U_), and then multiplied by the design effect for a stepped-wedge trial (DE_SW_). The sample size for a simple unadjusted trial was calculated as 1396 participants (effect size=3, SD of 20 for both groups, 80% power and 5% type I error). The DE_SW_ was 3.04 based on a formula provided by Hussy and Hughes, therefore sample size was 1396×3.04. We also inflated the total sample size considering 10% loss to follow-up. We then followed the approaches of determining the number of clusters required for total sample size considering a fixed cluster size of 60.^62^ We then calculated the number of steps that we need to randomise by dividing the total cluster by steps. We calculated that 16 MAR communities will be required for the study with four communities randomised to access MAR water in each step (figure 3).

### Data collection methods

The outcomes of interest will be measured from selected participants of 16 communities irrespective of their access to MAR water during five monthly visits. The interval between two successive blood pressure measurements or two consecutive data collection visits will be at least 4 weeks for each participant. After taking informed written consent from household heads and each participant, research staff will administer a survey using a structured questionnaire to collect information on drinking water sources, household members’ sociodemographic status, medical history, family history of cardiovascular diseases, medication intake, and cardiovascular risk factors including smoking history and alcohol intake during the first monthly visit. Exposure and outcome data will be collected in all five visits. Participants’ weight and hip circumference will be measured in all visits but height will be measured in one visit.

As part of the MAR uptake evaluation, the research staff will collect self-reported data on MAR water use from each household and whether households exclusively or intermittently use MAR water for drinking and cooking during follow-up visits. Research staff will also collect stored drinking and cooking water samples for measurement of electrical conductivity and will ask respondents the source of stored water.

### Exposure assessment

During each visit, research staff will inquire about household members’ reported primary water sources used for drinking and cooking purposes in the last 24 hours, collect reported information on whether participants exclusively used the primary water sources and explore whether any alternative water sources were used. They will also ask about the frequency of collection and cost of primary water sources for drinking and cooking, time required to collect water, amount of collected water and when the last water was collected. Research staff will observe the presence of stored water in households, ask the sources of each container of stored water and will collect water samples that have been stored for drinking and cooking (if any) to measure the salinity level, electrical conductivity, resistivity, total dissolve solutes and temperature using Hanna® Salinity meter. They will also collect the MAR water from the source MAR outlet to measure the salinity level, electrical conductivity, resistivity, total dissolved solutes and temperature. Research staff will collect 24 hours urine from each participant to measure the urinary sodium excretion as a proxy for sodium intake.^63 64^

### Outcomes assessment

Systolic blood pressure of the ≥20-year-old participants is the primary outcome of this study. Secondary outcomes will be diastolic blood pressure, mean arterial pressure and pulse pressure (table 1). The different components of blood pressure are independent cardiovascular risk factors associated with sodium intake,^65–69^ and indicate future risk for different cardiovascular diseases.^70^ High systolic blood pressure puts more stress on the vascular wall and is strongly associated with risk for future intracerebral haemorrhage, subarachnoid haemorrhage, angina, myocardial infarction and peripheral vascular diseases.^70^ Raised diastolic blood pressure is associated with aortic and thoracic aneurysm.^70^ Some effects of high sodium intake are independent of high systolic and diastolic blood pressures such as arterial stiffness and left ventricular mass─both are independent predictors of future cardiovascular diseases. High pulse pressure (difference between systolic and diastolic blood pressures) is associated with increased arterial stiffness,^66 68^ and high mean arterial pressure (diastolic blood pressure plus one-third of systolic blood pressure) and high pulse pressure are independently associated with increased left ventricular mass.^66 68^

**Table 1 T1:** Study outcomes including normal ranges of blood pressure and biomarkers

Outcomes	Study population		Measures	Normal range/calculation
	≥20 years old	Pregnant women		
Primary outcome: systolic blood pressure	Yes	Yes	Systolic blood pressure	90–140 mm Hg
Secondary outcomes: diastolic blood pressure	Yes	Yes	Diastolic blood pressure	60–90 mm Hg
Mean arterial pressure	Yes	Yes	Mean arterial pressure	Diastolic blood pressure + one-third systolic blood pressure
Pulse pressure	Yes	Yes	Pulse pressure	Systolic blood pressure − diastolic blood pressure
Tertiary outcomes: urinary sodium excretion	Yes	Yes	Urinary sodium-creatinine ratio	40–220 mEq/L/24 hours
Proteinuria	Yes	Yes	Urinary protein-creatinine ratio	<0.11 mg/mg

We will also measure the creatinine adjusted protein excretion of all participants as tertiary outcomes (table 1). Proteinuria is a biomarker for future risk of cardiovascular diseases,^71–74^ and is associated with the pathogenesis of cardiovascular diseases, including hypertension,^75 76^ chronic kidney disease,^77^ myocardial ischaemia,^78^ carotid artery thickness,^79 80^ left ventricular hypertrophy,^81 82^ hyperlipidaemia,^83^ atherosclerosis^84^ and coronary artery calcification.^72 80 85 86^ Reduced salt intake for 4 weeks has been associated with decreased proteinuria in blinded randomised controlled trial.^87^ Pre-eclampsia is associated with high maternal mortality and adverse pregnancy and fetal outcomes^38^ and is characterised by high blood pressure and proteinuria after 20 weeks of pregnancy.^88^

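### Mean arterial pressure, a secondary outcome, is defined with systolic pressure where pulse pressure belongs, so each value is too high by one third of the diastolic pressure

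*Protocol article*

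**What the plan says.** MAP is a declared secondary outcome in the protocol article's Outcomes assessment section: "Secondary outcomes will be diastolic blood pressure, mean arterial pressure and pulse pressure (table 1". Table 2 lists it again among the outcomes to be analysed.

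The article gives its formula twice, and the two statements agree:

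- Text of Outcomes assessment: "high mean arterial pressure (diastolic blood pressure plus one-third of systolic blood pressure".
- Table 1, calculation column: "Diastolic blood pressure + one-third systolic blood pressure".

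The same sentence of the text defines pulse pressure correctly: "High pulse pressure (difference between systolic and diastolic blood pressures". The pulse pressure row of Table 1, directly below the MAP row, does so too. No other definition of MAP appears in the article.

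**The concern.** The usual approximation to MAP adds one third of the pulse pressure to the diastolic pressure. The article adds one third of the systolic pressure instead. This is not a different convention. A mean pressure has to lie between the diastolic and systolic values, and the stated rule breaks that requirement at ordinary readings.

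If the rule is followed, a secondary outcome is wrong for every participant at every visit. The error is not a constant that drops out of a comparison between intervention and control periods. It is proportional to diastolic pressure, which is itself an outcome the intervention is meant to change. The estimated MAP effect would therefore be distorted whenever diastolic pressure responds, and the reported values could not be compared with MAP in other studies.

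**Working it through.** **Inputs.** The MAP and pulse pressure formulas come from Outcomes assessment and Table 1. The normal ranges, SBP 90–140 and DBP 60–90 mm Hg, come from Table 1. The planned systolic effect of 3 mm Hg comes from the Sample size section. The article gives no diastolic effect, so a range is assumed below.

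**The plan's own figure.** The article states no numerical MAP result to reproduce. The planning assumptions that supply the 3 mm Hg are "effect size=3, SD of 20 for both groups, 80% power and 5% type I error". They give 2 × (1.960 + 0.842)² × 20² / 3² ≈ 698 per group, or 1396 in total, which matches the stated unadjusted sample size. The MAP point does not depend on this figure.

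**Level error.**

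- Stated: DBP + SBP/3
- Conventional: DBP + (SBP − DBP)/3 = (2/3)DBP + (1/3)SBP
- Difference: DBP/3

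| Reading (SBP/DBP, mm Hg) | Stated | Conventional | Excess |
|---|---|---|---|
| 90/60 | 60 + 30 = 90.0 | 60 + 10 = 70.0 | 20.0 |
| 120/80 | 80 + 40 = 120.0 | 80 + 13.3 = 93.3 | 26.7 |
| 140/90 | 90 + 46.7 = 136.7 | 90 + 16.7 = 106.7 | 30.0 |

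The stated values are about 28% to 29% too high at these readings.

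**Internal check.** DBP + SBP/3 exceeds SBP whenever DBP is more than two thirds of SBP. At 90/60 and 120/80 DBP is exactly two thirds, and the supposed mean equals systolic pressure. At 110/80, within both normal ranges of Table 1, it is 80 + 36.7 = 116.7, which is above systolic pressure.

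**Treatment contrast.** Write ΔS and ΔD for the effects on systolic and diastolic pressure.

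- Stated rule: ΔD + ΔS/3
- Conventional rule: (2/3)ΔD + ΔS/3
- Difference: ΔD/3

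With ΔS = −3 mm Hg:

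| Assumed ΔD (mm Hg) | Stated | Conventional | Overstatement |
|---|---|---|---|
| 0 | −1.00 | −1.00 | 0% |
| −1 | −2.00 | −1.67 | 20% |
| −1.5 | −2.50 | −2.00 | 25% |
| −2 | −3.00 | −2.33 | 29% |
| −3 | −4.00 | −3.00 | 33% |

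If diastolic pressure moved the other way, by +1 mm Hg, the stated rule would give 0.00 where the conventional rule gives −0.33.

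**The case against.** There are four arguments for treating this as minor.

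1. **It does not touch the primary result.** The primary outcome and the sample size rest on systolic pressure alone. Diastolic pressure and pulse pressure are correctly specified, and no eligibility or success criterion in the article uses MAP. This stands in full.

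2. **It is recoverable.** The Blood pressure measurement section says that both pressures are recorded at every measurement, so MAP can be recomputed at any time and no data are lost. This also stands, but it helps only if someone notices the error.

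3. **It may be only a slip of wording.** The code is not shown, and the statement in the text is a gloss within a sentence about left ventricular mass. That the error will be programmed is therefore an inference. On the other side, Table 1 is where the article says how the outcome is calculated, it carries the same formula, and nothing corrects it.

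4. **The effect on inference may be small.** The stated rule inflates the variance as well as the effect. Take the planned systolic SD of 20, an assumed diastolic SD of 12 and an assumed correlation of 0.7. The SD is then √(144 + 44.4 + 112.0) = 17.3 under the stated rule and √(64 + 44.4 + 74.7) = 13.5 under the conventional one, a ratio of 1.28. A 25% larger effect over a 28% larger SD leaves the test statistic nearly unchanged. This is fair under those assumptions, so the main harm is a wrong estimate on a wrong scale, not a false-positive test.

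These points limit the consequences. None of them makes the formula correct.

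**Conclusion.** The formula is wrong as written, in both places. The level error is exactly one third of the diastolic pressure, 20 to 30 mm Hg over the article's normal diastolic range, and this needs no assumption. The error in the treatment contrast is exactly one third of the effect on diastolic pressure. Its size in percent depends on a diastolic effect that the article does not give: 20% to 29% overstatement for an assumed −1 to −2 mm Hg alongside the planned −3 mm Hg systolic, 33% if diastolic pressure also falls by 3, and none if it does not change. The damage is confined to this one secondary outcome. It should be corrected before the outcome is derived, because following the article gives a wrong result and the right formula is not in doubt.

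**What to change.** In the Outcomes assessment text and in the MAP row of Table 1, replace the formula with MAP = DBP + (SBP − DBP)/3, or equivalently (SBP + 2 × DBP)/3. Confirm that the derivation program uses this formula, and recompute any MAP values already derived under the printed rule.

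The cost is two text edits and a check of one line of code. No new data are needed, and no other outcome, the sample size or the analysis model has to change. The correction has no downside.
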